## Abstract

**Background:**

Parents of children with cancer experience a demanding situation and often suffer from psychological problems such as stress. Trying to coping with the complex body of information about their child’s disease is one factor that contributes to this stress. The aim of this study is to evaluate an intervention for person-centred information to parents of children with cancer that consists of four sessions with children’s nurses trained in the intervention method.

**Methods/Design:**

This is a multi-centre RCT with two parallel arms and a 1:1 allocation ratio. The primary outcome is illness-related parental stress. Secondary outcomes are post-traumatic stress symptoms, anxiety, depression, satisfaction with information, expected and received knowledge, and experiences with health care providers. A process evaluation is performed to describe experiences and contextual factors. Data are collected using web questionnaires or paper forms according to the parents’ preference, audio recording of the intervention sessions, and qualitative interviews with parents and the intervention nurses.

**Discussion:**

Few studies have evaluated information interventions for parents of children with cancer using large multi-centre RCTs. This intervention is designed to be performed by regular staff children’s nurses, which will facilitate implementation if the intervention proves to be effective.

**Trial registration:**

Clinical trials NCT02332226 (December 11, 2014).

## Background

Parenting a child with cancer is a stressful and demanding situation, and psychological problems such as stress, depression, and anxiety are more common in parents of children with cancer compared to parents of healthy children [1–3]. The difficulties experienced by parents are likely to be not only a consequence of the child’s disease as such, but can also be related to shortcomings in the encounter between these parents and the health care system. This study focuses on information, which should be an integral part of the care but nevertheless is often described as problematic by both parents and health care providers [4–6].

One of the challenges for these parents is to manage the complex and vast body of information available. Also, these parents have ranked their satisfaction with information low in comparison to other aspects of care such as professional skills, availability, and waiting times [7]. At diagnosis, a lot of information is conveyed to the parents, and health care professionals (HCPs) seem to be more attentive to parental needs at this time. However, further into the illness trajectory, parental needs and the HCPs’ focus change and the parents tend to experience less satisfaction with the information they receive [4, 6, 8–10]. Apart from the basic knowledge of the diagnosis and the planned treatment, parents need to look after central venous catheters, deal with the child’s nutrition, and monitor for complications and side effects. Much of this responsibility comes between treatment occasions when the family is out of the hospital [11]. Consequently, interventions for improved information are suggested as a means of protecting parents from excessive stress that in the long run could generate post-traumatic stress symptoms [12].

Although at times questioned, the concepts of family centeredness and child centeredness have had a significant influence in paediatric nursing [13–15]. These concepts imply that either the child or the family as a whole is in focus. However, research has shown that family members also have individual needs of, and preferences for, information [16]. This led us to apply a person-centred approach in this intervention. Using person-centeredness has been shown to improve satisfaction with care due to its individual tailoring of care to the person’s unique needs and to the involvement of the person in their own care [17]. We therefore chose to ground the intervention in this paper on the concept of person-centred information, which we have previously conceptualized as information about social, emotional, existential, and medical topics related to ill health and disease that is grounded in the person’s present knowledge, preferences, and needs and that seeks to empower the person to participate in the care of the sick individual [18].

The evidence base concerning interventions to improve parental wellbeing is not extensive [19, 20]. In general, available interventions tend to be psycho-educational in nature and to teach ways of coping rather than aiming at providing better information about the child’s disease [21–25]. Only a few studies have used interventions aimed specifically at improving and individualizing the information to parents, and the effect on psychosocial distress in those studies has not been consistent [18, 26, 27].

This paper describes an intervention for person-centred information for parents built on *The representational approach to patient education* [28]. Before starting this study, we completed a pilot study. Eight parents participated in the intervention, which was evaluated using a single-case experimental design and qualitative interviews. The pilot study showed that parents were appreciative of the intervention because it gave them an opportunity to discuss their own questions in depth. However, there were no changes in the outcome variables over time, which was likely due to a bias in sampling [18].

### Hypothesis and aims

The aim of this paper is to describe the design of a multi-centre randomized controlled trial that longitudinally evaluates an intervention with person-centred information for parents of children with cancer.

The hypothesis of the study described here is that an intervention with person-centred information emanating from the parents’ own information needs and their current knowledge is associated with reduced illness-related parenting stress, reduced post-traumatic symptoms, reduced depression, reduced anxiety, increased received knowledge, higher satisfaction with information, and reduced number of health care contacts among the participating parents compared to a control group that receives standard care.

A secondary aim of the study described in this paper is to explore the parents’ and intervention nurses’ experiences of participating in the intervention and to describe the contextual factors that influence the intervention’s effect.

## Methods/Design

### Design

The study is a multi-centre randomized controlled trial with two parallel arms and a 1:1 allocation ratio. One arm receives the intervention plus standard care, and the other arm only receives standard care according to local routines at each ward. In parallel to the intervention, a process evaluation is performed to describe experiences and contextual factors of importance, such as intervention dose and fidelity to the protocol.

Both quantitative data (questionnaires – either online or on paper according to the parent’s preference) and qualitative data (interviews, reflective notes, and audio recordings of the intervention meetings) are currently being collected and analysed. The questionnaires are sent out at baseline (T0), once during the intervention (T1), and at two weeks (T2), two months (T3), six months (T4), and one year (T5) after the intervention. A schedule of the intervention is provided in Table 1.

**Table 1 Tab1:** Weekly schedule of the trial

WEEK	0	4	6	7	8	11	14	20	22	24	30	46	74
Enrolment													
Diagnosis	X												
Eligibility screening		X											
Informed consent		X											
Allocation				X									
Assessments													
Baseline			T0										
Follow-up measurements								T1		T2	T3	T4	T5
Qualitative interviews^a^							Q1			Q2			
Recording of intervention meetings^a^					X	X	X		X				
Intervention													
Intervention meetings					X	X	X		X				

^a^With a subset of participants

### Participants

We are currently recruiting participants from two paediatric oncology tertiary care centres in Sweden. These centres cooperate with local hospitals where some of the treatment and supportive care is given; however, diagnoses and major treatments are performed at the centres. Inclusion criteria are being a parent of a child that a) is diagnosed with a first-time occurrence of a malignancy that is curatively treated and b) was diagnosed within the past two months. Furthermore, parents must be able to speak, read, and write Swedish well enough to participate without an interpreter.

All parents, including any stepparents, are being invited to participate, and interventions and measurements are being performed individually. Eligible parents are approached by a recruitment nurse at each site. After receiving information about the study, informed consent is obtained from parents willing to participate and the baseline questionnaire is distributed.

When the baseline questionnaire has been filled in, parents are randomized to one of the two study arms. Parents of the same child are randomized to the same arm to avoid contamination within couples. The allocation sequences were generated using the online service www.randomization.com. The allocation is performed by an independent person using opaque, pre-numbered envelopes. For each site, two strata are used: i) one participating parent per family and ii) two or more participating parents per family. This strategy will balance the number of parents equally between sites and arms. Both strata are blocked with randomized, varying block sizes (2, 4, or 6 units) that are blinded to the researchers and the person performing the allocation.

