### Sample size

According to a power calculation, 130 parents in total will be needed if we expect a moderate effect size (Cohen’s *d* = .5, which corresponds to 13 points of the total score of the primary outcome measure, the Pediatric Inventory for Parents (PIP)), α = .05, and statistical power = .8. We expect that 30 % of parents will not finish the study, meaning that 180 parents in total need to be recruited.

For the qualitative interviews, we plan to interview one third of the parents (*n* = 20) allocated to the intervention arm.

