### Data analysis

Quantitative data will be analysed using the SPSS statistical software package. Continuous variables will be reported as the arithmetic mean ± standard deviation, and categorical variables will be reported as the frequency and percentage. Differences between the trial arms will be evaluated using Student’s *t*-test for the outcome variables at the available time points. We will also perform regression analyses using data from the process evaluation, including intervention fidelity and other contextual factors. By using multivariate techniques, we will adjust for any differences found in the baseline characteristics of the participants. When appropriate, Bonferroni adjustments will be made on the overall significance levels. For all of these analyses, effect sizes will be calculated. All analyses will employ the intention to treat principle, and two-tailed *p*-values ≤ .05 will be considered as statistically significant [36].

Qualitative data, such as individual and focus groups interviews and recorded intervention meetings, will be analysed using qualitative content analysis [37]. This method focuses on similarities and differences in data, which is useful for finding possible variances in intervention performance that might explain differences in outcomes.

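### Families are randomised, but the sample size and Student's t-test treat parents as independent, so alpha .05 and power .8 are not both delivered

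*Protocol article*

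**What the plan says.** Three statements in the protocol article bear on this point.

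- **Participants.** Allocation is by family: "Parents of the same child are randomized to the same arm to avoid contamination within couples". Families with several participating parents are expected, because "All parents, including any stepparents, are being invited to participate, and interventions and measurements are being performed individually". At each site the strata are "i) one participating parent per family and ii) two or more participating parents per family".
- **Sample size.** The count is in parents: "According to a power calculation, 130 parents in total will be needed if we expect a moderate effect size". The effect is d = .5, 13 points on the Pediatric Inventory for Parents (PIP), with alpha .05 and power .8. The increase to 180 recruited parents is for 30% non-completion only.
- **Data analysis.** The arms are compared with Student's t-test "for the outcome variables at the available time points". The section also mentions regressions on process-evaluation data and adjustment for baseline differences. None of these is said to contain a family term.

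**The concern.** The unit of randomisation is the family, but the unit of the calculation and of the test is the parent. Two parents of one child share the diagnosis, the treatment course and often the household. The PIP measures stress arising from that illness, so their scores are very likely to be positively correlated. When correlated parents sit in the same arm, the variance of the arm difference is larger than the t-test assumes.

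Two consequences follow, and they belong to different analyses:

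- The t-test as named rejects a true null hypothesis more than 5% of the time, and its confidence intervals are too narrow.
- A valid test on the same parents has less than the stated power.

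The problem affects the primary PIP comparison and the parent-reported secondary outcomes at every time point, and it raises the chance of a false claim of benefit.

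**Working it through.** **Inputs from the article:** d = .5, two-sided alpha .05, power .8, 1:1 allocation, 130 parents (65 per arm), 30% non-completion, 180 recruited.

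**Inputs not in the article (assumptions):** the share p of families contributing two parents, and the ICC. No family is taken to contribute more than two parents; larger families would raise the design effect.

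**1. Reproduce the stated figure.** A two-sample t-test on independent observations needs 63.8 per arm, so 64 per arm and 128 in total. At 65 per arm the power is .808. The stated 130 is this number, slightly rounded up, and contains no allowance for clustering.

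**2. Design effect.** DE = 1 + (Σm²/Σm − 1) × ICC, where m is the number of parents in a family. With m equal to 1 or 2, Σm²/Σm = (1 + 3p)/(1 + p).

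- p = .5, ICC .2: (2.5/1.5 − 1) × .2 = .133, so DE = 1.133
- p = .7, ICC .4: (3.1/1.7 − 1) × .4 = .329, so DE = 1.329
- p = 1, ICC .5: (4/2 − 1) × .5 = .5, so DE = 1.50

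**3. Consequences for 130 completing parents.** The effective number is 130/DE. The power of a valid test uses 65/DE per arm. The true type I error of the plain t-test is approximately 2 × [1 − Φ(1.96/√DE)]. Completers needed for 80% power are 128 × DE.

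| Two-parent families, ICC | DE | Effective parents | Power, valid test | Type I error, plain t-test | Completers needed |
|---|---|---|---|---|---|
| 50%, .1 | 1.067 | 122 | .78 | .058 | 137 |
| 50%, .2 | 1.133 | 115 | .756 | .066 | 145 |
| 70%, .4 | 1.329 | 98 | .687 | .089 | 170 |
| 100%, .5 | 1.50 | 87 | .633 | .110 | 192 |

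**4. Simulation check.** Simulating the plain t-test at 65 per arm gave type I errors of about .067, .09 and .11 for the last three rows, which agrees with the formula. Its rejection rate at d = .5 was about .79, .78 and .77. The plain t-test therefore appears to keep most of its power, but only because its type I error is inflated.

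**5. Baseline adjustment.** If baseline PIP has correlation r with the outcome, the standardised effect becomes .5/√(1 − r²). The stated 30% loss leaves 180 × .7 = 126 completers, 63 per arm. The same DE is applied to the adjusted outcome.

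- r = .5, DE 1.3: .5/√.75 = .577, effective 63/1.3 = 48.5 per arm, power .80
- r = .5, DE 1.5: power .74
- r = .3, DE 1.3: power .72

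**The case against.** - **A full analysis plan may deal with clustering.** It may, but the article does not leave the test open. It names one that does not match its own allocation, and the sample size reproduces under the same independence assumption.
- **Alpha and power do not fail in the same analysis.** This is correct. The t-test inflates alpha and keeps its rejection rate near .77 to .79; the fall to .76–.63 applies to a valid test. What fails is the joint promise of alpha .05 and power .8.
- **The range leans high.** This stands in part. At an ICC of .1 with half the families contributing two parents, type I error is only .058 and power .78. The upper end assumes that every family contributes two parents, although a single-parent stratum exists. Non-completion also breaks pairs. If parents drop out independently, a completer's partner also completes 70% of the time. DE then runs from 1 + .667 × .7 × .2 = 1.09 to 1 + .7 × .5 = 1.35, power from .77 to .68, and type I error from .061 to .092. Partners who leave together would bring these back towards the table.
- **Ignoring the stratification makes a t-test conservative.** To the extent that site and family type predict outcome, this offsets some of the inflation. The article does not allow it to be quantified.
- **Regaining .80 through baseline adjustment is not assured.** This stands; it depends on r and DE, as step 5 shows.

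These points reduce the size. They do not change the direction or the remedy.

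**Conclusion.** The concern holds. For any positive within-family correlation, the named test and the stated power are wrong for the allocation described. The direction follows from the article itself; the size does not, because the ICC and the family mix are not given. For an ICC of .2 to .5 and 50% to 100% two-parent families with pairs intact, the plain t-test runs at a type I error of about .066 to .11, and a valid test on 130 completers has power of about .76 to .63. A smaller ICC, or pairs broken by dropout, brings the figures closer to nominal. An ICC of zero would remove the problem, but that is implausible for illness-related stress in parents of the same child. It must be fixed, because it affects the primary inference and the correction costs almost nothing.

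**What to change.** Replace Student's t-test, for PIP and the secondary outcomes, by a method that respects the family. This can be a linear mixed model with a random intercept for family, or GEE or cluster-robust standard errors by family. Include arm, site and the one versus two-or-more-parent stratum, and preferably the baseline value of the outcome.

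In the Sample size section, state an assumed ICC and mean number of parents per family. Restate the power for 130 completers, and for the 126 that 180 recruits leave after 30% loss, over a range of both. If baseline PIP is used to recover power, show that figure over a range of r as well.

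The cost is analysis wording and a recalculated power figure. SPSS, the package already named, fits the mixed model, and allocation already requires parents to be identified by family. No data or participants are added. The intervals will be wider, and the restated power may fall below .8.

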### Sample size

According to a power calculation, 130 parents in total will be needed if we expect a moderate effect size (Cohen’s *d* = .5, which corresponds to 13 points of the total score of the primary outcome measure, the Pediatric Inventory for Parents (PIP)), α = .05, and statistical power = .8. We expect that 30 % of parents will not finish the study, meaning that 180 parents in total need to be recruited.

For the qualitative interviews, we plan to interview one third of the parents (*n* = 20) allocated to the intervention arm.

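### The recruitment target of 180 does not follow from 130 completers and 30% attrition, which give 186; the effect on power is negligible and one corrected sentence settles it

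*Protocol article*

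**What the plan says.** The Sample size section of the protocol article gives the requirement first: "According to a power calculation, 130 parents in total will be needed if we expect a moderate effect size". The effect size is Cohen's d = .5, "which corresponds to 13 points of the total score of the primary outcome measure", the Pediatric Inventory for Parents. The remaining inputs are "α = .05, and statistical power = .8".

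The allowance for loss comes next: "We expect that 30 % of parents will not finish the study". The same sentence then draws its conclusion, that this share "of parents will not finish the study, meaning that 180 parents in total need to be recruited". So 180 is presented as the direct result of 130 and 30%. The article gives no other attrition rate and no other base sample size, and it does not call 180 approximate.

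Two other sections bear on the calculation. The Design section describes a "multi-centre randomized controlled trial with two parallel arms and a 1:1 allocation ratio". The Data analysis section names Student's t-test for comparing the arms, with a two-tailed criterion of 5%.

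**The concern.** A recruitment target that allows for loss should return the required number of completers once the expected loss is taken off. Here it does not: 180 less 30% is 126, not 130. One of the three printed figures must be something other than what the article says it is.

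What is at stake is mainly clarity. If loss runs exactly as expected, the trial meets its recruitment target and still misses its stated requirement. A reader then cannot tell which figure the trial is committed to: 130 completers, 180 recruits or a tolerated loss of 30%. It is also fair to ask whether the shortfall costs power, so that is checked below.

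**Working it through.** **Inputs.** All are from the protocol article.
- From Sample size: 130 parents needed, d = .5 (13 points, so an implied SD of 13/0.5 = 26), α = .05, power .8, attrition 30%, recruitment target 180.
- From Design: 1:1 allocation.
- From Data analysis: two-tailed testing with Student's t-test.

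**Step 1: the base figure of 130.**
- Normal approximation: n per arm = 2(z₀.₉₇₅ + z₀.₈₀)²/d² = 2(1.960 + 0.842)²/0.25 = 62.8, so 63 per arm and 126 in total.
- Two-sample t-test (noncentral t): 63.8, so 64 per arm and 128 in total.

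The stated 130 is the t-test answer with a margin of two. The base figure is sound for independent parents.

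**Step 2: the step from 130 to 180.**
- The usual inflation, N/(1 − loss): 130/0.70 = 185.7, so 186. Check: 186 × 0.70 = 130.2.
- The common mistaken form, N × (1 + loss): 130 × 1.30 = 169.

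Neither gives 180.

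**Step 3: what 180 does imply.**
- Completers at 30% loss: 180 × 0.70 = 126, which is 130 − 126 = 4 short.
- Loss at which 180 leaves 130: 1 − 130/180 = 27.8%.
- Base figures that lead to 180 or near it at 30% loss: 126/0.70 = 180 exactly; 128/0.70 = 182.9, so 183.

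The target is therefore what the normal-approximation requirement of 126 would give, but the article states 130.

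**Step 4: the effect on power.** Two-sided α = .05, d = .5, equal arms, parents treated as independent:

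| Completers | Per arm | t-test | Normal approximation |
|---|---|---|---|
| 126 | 63 | .795 | .801 |
| 128 | 64 | .801 | .807 |
| 130 | 65 | .808 | .813 |

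Moving from 130 to 126 completers costs .808 − .795 = .013 by the t-test and .813 − .801 = .012 by the normal approximation, a little over one percentage point either way.

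**The case against.** The best defence is that nothing of substance is lost.

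- **Power.** The article gives power to one decimal. At that precision 126 completers deliver it by either method, and by the normal approximation 126 is exactly the number required. The sample-size text does not say which formula was used.
- **Margin.** The base of 130 already exceeds the t-test requirement of 128 by two, so half of the four-completer shortfall is only that margin.
- **Uncertainty of the inputs.** The 30% is a forecast. The distance between it and 27.8% is smaller than the likely uncertainty in any such forecast.
- **Timing.** The loss refers to parents who do not complete the study, and the last questionnaire comes one year after the intervention. The arms are to be compared at each available time point, so the earlier comparisons may have more than 126 respondents.

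All of this stands as an argument about consequence. It does not make the figures agree. Rounding does not account for 180, because 185.7 to the nearest ten is 190 and 27.8% rounds to 28%. If 126 was the true base, then the stated 130 is the figure that needs correcting. The fact that an article condenses a longer protocol may explain an omission, but here all three figures are printed and they conflict.

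A reader might infer something stronger: that the trial is underpowered by its own plan, or that it must enrol six more parents to reach .8. The documents do not support this. The 186 is what 130 completers would take, not what power of .8 would take. At 30% loss, .8 needs 183 recruits by the t-test and 180 by the normal approximation. Nor should the point borrow weight from the clustering of parents within families, which is a separate question and does not enter these figures.

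**Conclusion.** The point holds as an internal inconsistency of low severity. The three figures 130, 30% and 180 cannot all be right: the first two lead to 186, and the last two lead to 126. The gap is six recruits or four completers, and no other section of the article reconciles it.

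The consequence for power is just over one percentage point relative to 130, and the target of 180 still gives about .80 at the stated effect size. This rests on the article's own d, α and attrition, on equal arms, and on parents counted as independent observations. Neither the design nor the planned analysis needs to change on this account.

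**What to change.** Correct the sentence without enrolling more parents, in one of two ways:

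1. Keep 180 and state that at 30% attrition it yields about 126 completers, with power of about .80 before any allowance for family clustering (.795 by the t-test, .801 by the normal approximation).
2. Keep 180 and 130, and state that the target covers attrition of about 28%.

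With either wording, note that 186 is the figure that follows from 130 and 30%, so that readers can see how the numbers relate. The cost is one sentence. The first option carries a slightly less favourable stated figure; the second, a slightly smaller allowance for loss.
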